#### Inclusion/exclusion criteria

Extremely premature infants are eligible for the study if they meet the following inclusion criteria: birth weight < 1250 g; mother plans to pump and provide milk for at least 2 months; absence of severe congenital anomalies; NICU admission ≤ 24 hours of life; ability to begin protocol within 96 hours of life. The exclusion criteria are as follows: birth asphyxia (cord pH/arterial pH < 7.0); presence of a tracheoesophageal fistula, maternal + HIV status, maternal drug or substance use that precludes infant from receiving mother’s milk, triplets or higher order multiple births.

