#### Participant recruitment, enrollment and informed consent

The collaborating sites have a relatively high census of extremely premature infants yearly and very high lactation initiation rates (80–90 %) which facilitates subject recruitment. Mothers on bed rest protocols in the high risk antenatal unit, who meet inclusion criteria (estimated fetal weight < 1250 g per prenatal ultrasound) are approached and invited to participate. In our pilot studies, this recruitment strategy was highly successful and the majority of women approached agreed to participate. Mothers who deliver without significant time in the antenatal unit are approached within 96 hours after delivery.

The principal investigator (PI) and/or research nurse explain the study in detail, answer questions, and leave the consent form so that the mother can read it and discuss the study with her family prior to enrolling. A second meeting is scheduled later that same day, when convenient for the mother, and the PI and/or research nurse return and answer any additional questions. Informed consent is obtained at this time (second meeting) if the mother decides to participate. This precaution is taken because these women are considered psychologically vulnerable, in terms of research. Mothers are informed that their care (or their baby’s care) will not be affected if they decide not to participate in this study. In addition, mothers are informed that they have a right to withdraw their infant (or themselves) from the study at any time and for any reason without compromise to their care, or their infant’s care.

If the woman is approached antenatally, before securing informed consent, the PI and/or research nurse explain to her that if she remains pregnant and the estimated fetal weight (EFW) is over 1250 g per prenatal ultrasound, then the infant, once born, will no longer qualify for the study. This is deemed a screen failure since the infant will no longer meet inclusion criteria. All women are assured that their infant’s care, and their breastfeeding support post-birth, will not be affected by their decision to participate in the study, or if they become ineligible. Since 27 % of enrolled mothers are expected to be Hispanic, Spanish-IRB-approved translations of study documents are available at all sites.

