#### Randomization

A 1:1 blocked randomization scheme was utilized to yield “comparable” subjects in each of the 2 groups, stratified by birthweight (<750 g, 751–999 g, 1000–1250 g) within each site, to avoid imbalance in the distribution of the 2 groups at each site. We produced a separate block randomization list within each site for each subgroup (a total of three strata). The randomization is based on permutated blocks with random sizes varying from 2 to 4 (to avoid guessing) to make sure that each site will have an equal number of participants in each group. The randomization list was generated prior to study initiation using a random seed number via SAS PROC PLAN (SAS Inc., Cary, NC, USA) to generate the stratified randomization design. The statistician prepared sealed, numbered opaque envelopes for each site, with randomization assignment inside. The envelopes were given to the site’s research coordinator who assures that they are used in numerical order. After informed consent is obtained, the research coordinator opens an envelope, removes the group assignment form, writes the infant’s study ID # and date on the form, makes a copy of the form and sends it to the statistician, keeping the original in the infant’s study file. Group A (treatment) infants receive OMM, while Group B (control) infants receive a placebo (sterile water). In the case of a multiple birth, twins are stratified and randomized into either the intervention or the control group, and will be analyzed independently between the two experimental groups. Triplets or higher order multiple births are not be eligible for the study.

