#### Study procedures

##### Collection of milk

Research personnel within each site have been trained, using a standardized protocol (Protocol version 4; Dated 1/5/2015), to assure coherence of data collection. Mother’s milk samples are collected during the routine expression of milk, using a hospital-grade electric breast pump, and are stored in the NICU breastmilk refrigerator. When at least 2.5 mL (½ teaspoon) of mother’s milk is available, the research nurse prepares the syringes for the first 24 hours of the Initial Treatment Period. For infants in the placebo group, the milk is immediately frozen, in a separate NICU breastmilk freezer to maintain blinding, for later use when enteral feedings are started. Using sterile gloves, 24 sterile oral syringes are each filled with 0.1 mL of OMM or sterile water (based on group assignment), capped, and covered with a white tape as a blinding procedure. Each syringe is labeled with the patient’s name, medical record number, and the date and time of preparation. Syringes are prepared in the same sterile manner, by the research nurse, every 24 hours. For the Extended Treatment Period, a total of 16 syringes are prepared daily, for treatments to be given every 3 hours.

It is standard practice to encourage mothers of extremely premature infants to pump frequently (typically every 3 hours) in order to establish and maintain an abundant milk supply. Therefore, it is common for NICU nurses to see several containers, with varying amounts of mother’s milk, in the NICU refrigerator, on a daily basis. The milk is either used for enteral feeds or frozen for storage. Since only miniscule volumes of milk are needed daily for this intervention (2.4 mL and 1.6 mL per day, for Initial and Extended Treatment Periods, respectively) it has been our experience that NICU nurses do not notice that a small volume of milk has been removed from the refrigerator, and thus they remain blind to group assignment.

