##### Oropharyngeal administration procedure

Using a standardized protocol, the nurse provides the dosing as follows: two syringes are warmed to room temperature. The first syringe’s cap is removed and the tip of the syringe is gently placed into the infant’s mouth, alongside the right buccal mucosal tissue. The syringe tip is directed posteriorly towards the oropharynx, and the total volume (0.1 mL) is slowly administered, over at least 1 minute. The second syringe is placed in the infant’s mouth in the same manner, but alongside the left buccal mucosal tissue. The entire volume (0.1 mL) is administered slowly, over at least 1 minute. A petite swab is used to carefully swab the right buccal mucosal tissue, followed by the left buccal mucosal tissue (≤5 seconds each side). A total volume of 0.2 mL is administered per treatment, with buccal swabbing taking place over 10 seconds. Vital signs are carefully monitored throughout the procedure. The procedure is repeated every 2 hours for 48 consecutive hours during the Initial Treatment Period, which begins within the infant’s first 96 hours of life. The Extended Treatment Period begins immediately after the Initial Treatment Period has been completed and ends when the infant reaches 32 weeks CGA as depicted in Fig. 2. Dosing is provided every 3 hours during the Extended Treatment Period. Participation in this study does not interfere with the initiation or progression of enteral feedings, which is left to the discretion of the attending physician. Urine, oral mucosal swabs, and stool specimens are collected from enrolled infants, and milk samples from their mothers, at specific time points, as depicted in Fig. 2.

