Primary endpoints: L-OS is defined as the new onset of at least 2 clinical symptoms with a positive blood culture (noted after Day of life 3) and identification of an organism known to be a cause of sepsis rather than a contaminant. If the blood culture shows a potential contaminant (such as *Staphylococcus epidermidis*) a second blood culture is obtained to confirm the presence of bacteremia.

Secondary endpoints: NEC and death. NEC is defined according to modified Bell’s criteria stage > 2 with clinical signs and radiological evidence including any of the following: pneumatosis intestinalis, portal venous gas with or without pneumoperitoneum.

Covariates: sex, gestational age and birth weight will be included as covariates.

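### The late-onset sepsis endpoint is timed from birth and not from randomisation, so an infection that precedes randomisation in a late-starting infant can count as a primary event

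*Protocol article*

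**What the plan says.** Outcome measures for specific Aim 1 gives three conditions for late-onset sepsis:

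- "new onset of at least 2 clinical symptoms with a positive blood culture (noted after Day of life 3");
- "identification of an organism known to be a cause of sepsis rather than a contaminant";
- for a possible contaminant, "a second blood culture is obtained to confirm the presence of bacteremia".

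Entry is described in other sections:

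- Inclusion/exclusion criteria requires "ability to begin protocol within 96 hours of life". The exclusions listed there do not include sepsis or a positive culture before entry.
- Participant recruitment, enrollment and informed consent: "Mothers who deliver without significant time in the antenatal unit are approached within 96 hours after delivery". Consent is then taken at a second meeting later that day.
- Randomization: "After informed consent is obtained, the research coordinator opens an envelope".
- Collection of milk: once 2.5 mL of milk is available, "the research nurse prepares the syringes for the first 24 hours of the Initial Treatment Period".
- Oropharyngeal administration procedure: dosing is repeated "during the Initial Treatment Period, which begins within the infant’s first 96 hours of life".

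Statistical analysis specifies intention to treat. No section links the start of the endpoint window to randomisation, and none says whether the day of birth is day 0 or day 1.

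**The concern.** An outcome event should be able to occur only after assignment. Here the endpoint window opens at a fixed age, while assignment happens at a varying age that can be later. An infant whose symptoms and culture fall between the two meets the definition, is not excluded, stays in the intention-to-treat set, and so counts as a primary event that treatment could not have prevented.

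The word *noted* adds a second uncertainty. It can be read as the day the culture was drawn or the day its result was reported. Five sites could classify the same infant differently.

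At stake are a small dilution of the primary comparison and an endpoint that can be read in more than one way. The sample size is set at exactly 80 % power, so there is no reserve.

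**Working it through.** **1. Length of the overlap.** The latest first dose is at 96 h, and randomisation comes before it, so 96 h is also the practical limit for randomisation.

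- Birth = day 1: day 3 ends at about 72 h. Overlap: 96 − 72 = 24 h at most (somewhat more if calendar days are counted).
- Birth = day 0: day 3 ends at about 96 h. The overlap nearly closes. What remains is a culture drawn before randomisation and reported later, if the result date counts.

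**2. The plan's own figure.** Inputs from Sample size/Power analysis: 20 % versus 10 %, two-sided alpha 0.05, power 80 %, R² = 0.2.

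n per arm = [1.96·√(2·0.15·0.85) + 0.8416·√(0.2·0.8 + 0.1·0.9)]² / 0.10² = (0.990 + 0.421)² / 0.01 ≈ 199

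Total 398; 398 / (1 − 0.2) = 497.5, so 498, as stated. With 20 % dropout, 498 / 0.8 = 622.5, against 622 stated. The plan's figures reproduce.

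**3. A plausible share of events (assumption).** The article gives no rate for this window. Suppose a constant hazard from day 3, and suppose every infant is randomised at the latest time, which overstates the exposure. A one-day overlap then holds 1/(T − 3) of the events, where T is the follow-up in days.

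- T = 119 (17 weeks, the upper length of stay in the Background): 1/116 = 0.9 %, or 0.17 points of the 20 %.
- T = 84 (12 weeks, the lower length of stay): 1/81 = 1.2 %, or 0.25 points.
- T = 28 (all events within four weeks): 1/25 = 4.0 %, or 0.8 points.

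A range of x = 0.2 to 1 point covers these cases. With 249 analysed per arm, that is 0.5 to 2.5 infants per arm. Earlier clustering of events would raise the share; earlier randomisation would lower it.

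**4. Effect on power.** Let x be the part of the 20 % that precedes randomisation, with the remainder halved by treatment.

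- Events counted as now worded: p1 = 0.20, p2 = x + (0.20 − x)/2.
- Events removed by the fix: p1 = 0.20 − x, p2 = (0.20 − x)/2.

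Power = Φ{[(p1 − p2)·√n − 1.96·√(2·p̄·(1 − p̄))] / √[p1(1 − p1) + p2(1 − p2)]}, with p̄ the mean of p1 and p2 and n = 249 × 0.8 = 199.2 per arm.

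| x (points) | p2 as worded | Odds ratio | Power as worded | Power after fix | Recovered |
|---|---|---|---|---|---|
| 0 | 10.0 % | 0.444 | 80.0 % | 80.0 % | 0 |
| 0.2 | 10.1 % | 0.449 | 79.1 % | 79.6 % | 0.4 |
| 0.5 | 10.25 % | 0.457 | 77.7 % | 78.9 % | 1.1 |
| 1.0 | 10.5 % | 0.469 | 75.3 % | 77.6 % | 2.3 |
| 2.0 | 11.0 % | 0.494 | 70.1 % | 75.0 % | 4.9 |

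The recovered column is taken from unrounded powers. The fix does not restore 80 % because removing these events also lowers the control rate. The 2-point row shows sensitivity only: it is 2.5 times the largest share found in step 3.

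**The case against.** The strongest defence is that this is an operational detail. The endpoint is named late-onset and asks for new symptoms, so any site would use the draw date, and a day-of-life convention is something an article may leave to the full protocol. That stands for the convention and for the meaning of *noted* taken alone. It does not answer the main point: the article itself states an age-based endpoint, a 96-hour entry limit and a list of exclusions, and these rules combine to admit an event before randomisation.

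The defence is right on the following limits, where a reader might infer more than the article supports:

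- **That any positive culture counts.** It does not. Two new symptoms and a non-contaminant organism are also required.
- **That every infection before treatment is misplaced.** Infections between randomisation and first dose belong in an intention-to-treat analysis. Only those before randomisation do not.
- **That all infants are exposed.** Only late starters are. Some mothers consent antenatally: the Discussion reports 11 screen failures arising from antenatal consent among 77 enrolled.
- **That the comparison is biased toward an arm or the type I error inflated.** Pre-randomisation events cannot depend on assignment and balance in expectation.
- **That power falls to about 70 %.** This needs 2 of the 20 points to precede randomisation, which nothing in the article suggests.

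**Conclusion.** The point holds in limited form. As worded, the primary endpoint can count an infection that precedes randomisation. The window for this is at most about 24 hours if birth is day 1, nearly nothing if birth is day 0, and concerns late-starting infants only. The consequence is dilution toward no effect. With 0.2 to 1 point of the 20 % affected, power is about 79 to 75 % instead of 80 %, and rewording the endpoint recovers roughly 0.5 to 2 points. These figures rest on an assumed share, since the article gives no rate, and on the plan's halving of risk applying to all remaining events. The validity of the test is not threatened. The change is still worth making because it concerns the primary endpoint, costs little and removes two ambiguities.

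**What to change.** Amend the endpoint definition as follows.

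- State whether the day of birth is day 0 or day 1.
- Count a primary event when the existing symptom, culture and organism criteria are met, the culture was **drawn** after day of life 3 and after randomisation, and symptoms began after randomisation.
- Keep all randomised infants in the intention-to-treat set. For an infant infected before randomisation, count only a new, later episode.
- Keep events between randomisation and first dose as primary events.
- Report positive cultures before randomisation by arm as a baseline characteristic.

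Cost: a short amendment, with no new patients or procedures. It needs the culture draw time, which should be in the hospital record (an assumption), and the time of randomisation. The Randomization section mentions only a date on the assignment form, so a clock time or a same-day rule is needed. Recruitment was under way with 77 enrolled when the article was written, and the investigators and data analyst are described as blinded, so the definition could be settled without knowledge of results by arm. The downside is slightly fewer counted events.

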## Background

Despite advances in neonatal medicine, extremely premature (birth weight < 1250 g) infants have substantial mortality and morbidity, often resulting from infectious morbidities including late-onset sepsis (L-OS) and necrotizing enterocolitis (NEC) [1–8].

L-OS is highly prevalent (32–53 %) [6, 7], and costly (approximately US $23,317 per episode) [8] for this population. NEC accounts for an estimated US $6.5 million in additional hospital costs yearly, in the United States [3]. The risk for acquiring NEC is inversely related to birth weight; therefore, extremely premature infants have the highest incidence (10–12 %) of NEC, as well as the highest NEC-associated mortality rates [4]. With increased survival of premature infants, even a modest reduction in the incidence of L-OS and NEC could yield a substantial cost savings, and improved health outcomes for these infants. Minimizing these devastating infections takes on a greater urgency – *starting with the first days of life.*

L-OS is common in extremely premature infants because they are functionally immunodeficient, have an immature intestinal mucosal barrier [9–11], and require multiple invasive lines as part of their care. Pathogenic (intestinal) bacteria are able to translocate across the immature epithelial barrier and gain access to the bloodstream, while invasive catheters allow pathogenic bacteria a simple point of entry into the circulation. While Gram-positive organisms (particularly coagulase-negative *Staphylococcus* spp.) tend to be the predominant pathogens causing L-OS in this population, Gram-negative bacilli account for up to 30 % of episodes [12].

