NEC, like L-OS, is associated with significant mortality and long-term morbidities for extremely premature infants. NEC is an inflammatory bowel necrosis which involves mucosal injury, altered intestinal microbiota, an unbalanced pro-inflammatory response, and abnormal host defense [4]. NEC is common in extremely premature infants because they have an immature intestinal epithelial barrier that is vulnerable to injury, a gastrointestinal microbiota which has a predominance of potential pathogens, an unbalanced pro-inflammatory response to pathogenic bacteria by immature enterocytes, decreased tight junctions between epithelial cells (permitting the translocation of pathogens) and an immature host defense system [4, 5, 13].

Pathogenic colonization of the preterm gut appears to be a primary step in the pathogenesis of both L-OS and NEC [5, 13, 19–21]. A pathogen-predominant microbiota promotes injury to the mucosal barrier and facilitates bacterial translocation from the gut into the bloodstream [22]. Recent research suggests that specific pathogens colonize the preterm gut before they invade the bloodstream with subsequent L-OS, confirming the importance of abnormal microbiota with subsequent mucosal translocation as an important pathomechanism [22, 23]. Therefore, optimizing the intestinal microbiome in extremely premature infants could reduce the risk of L-OS, and also NEC. Methods to enhance beneficial bacteria and improve microbial diversity may decrease the risk for L-OS and NEC via multiple mechanisms. Exposure to mother’s milk post-birth can reduce colonization by pathogenic organisms and increase commensal bacteria, reducing bacterial translocation, modulating the inflammatory response and decreasing intestinal injury [24–27].

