##### Sample size/Power analysis

We hypothesize that extremely premature infants who receive oropharyngeal administration of mother’s milk will have a significantly lower incidence of L-OS (primary endpoint). Based on recent (2012) data from the Vermont-Oxford Network that included > 20,000 ELBW infants, the incidence of L-OS in this population was 19.4 %. Based on data from Manzoni et al. [14], that showed a reduction of L-OS from 17 % to 6 % with exogenous bovine lactoferrin in preterm infants, we conservatively estimate a reduction in L-OS from 20 % to a total of 10 % in milk-treated infants. Since Manzoni et al. [14] used a lactoferrin dose similar to that in mother’s milk, and based on studies that mother’s milk reduces L-OS [6–8] this effect size of reduction (from 20 % to 10 %) should be realistic and obtainable given the patient population. Since many variables may alter the risk for L-OS in extremely premature infants multivariable logistic regression (for dichotomous L-OS outcome) will be performed adjusting for covariates such as sex, gestational age and birth weight. Power calculations were determined using PASS 14.0 software (NCSS, LLC, Kaysville, UT, USA). We estimate that up to a total of 10 covariates will account for a combined 20 % (*R*^*2*^ = 0.2) of variance in the regression model. Based on a 2-tailed alpha of 0.05 and 80 % power, a sample size of 498 (249 in each group) will be needed to reach a statistical power of 80 % to detect a difference of 10 % versus 20 % (effect size odds ratio (OR) = 0.44) in L-OS outcome between milk and placebo groups. Therefore, the study is adequately powered for the primary endpoint L-OS. The study sample is being accrued from 5 sites and, based on a lactation initiation rate of > 70 % for all sites (conservative, based on actual rates of 80–90 %), and an estimated refusal rate of 30 % (a conservative estimate based on our previous experience in recruiting subjects for this intervention), we will screen a total of 1270 patients to enroll 622, with an estimated dropout rate of 20 %, that will allow us a complete analysis for 498 subjects.

##### Outcome measures for specific Aim 1

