##### Statistical analysis

Statistical analysis will be performed using an intention-to-treat (ITT) approach. Baseline infant and mother demographics and clinical characteristics will be summarized between milk and placebo groups using a chi-square or Fisher exact test for categorical variables (i.e. infant gender, race/ethnicity, socioeconomic status, maternal diagnosis of pre-eclampsia, premature and/or prolonged rupture of membranes, delivery mode, and steroid administration) and an independent *t* test or a Wilcoxon two-sample test for continuous variables (i.e. the time of initial exposure to mother’s own milk, duration [number of days] of central line placement and mechanical ventilation, gestational age, birth weight, post-natal steroids, antibiotic duration), depending on satisfying the normality assumption or not, respectively. A multivariable logistic regression with L-OS or NEC or death as the dependent variable, and group (milk versus placebo) as the primary independent variable will be constructed to assess the strength of association between oropharyngeal milk treatment and risk of L-OS or NEC or death, adjusting for pre-specified covariates including sex, gestational age and birth weight. Odds ratios and corresponding 95 % confidence intervals will be reported. Because the amount of mother’s milk that enrolled infants receive as a “feeding” will affect our study endpoints, we will closely monitor and record the total amount of mother’s milk received (percent of total feeding volume) for each study subject. We do not anticipate the amount of milk the infant receives as an enteral feed will be affected by group assignment. However, if we do observe a significant difference between the intervention and placebo groups, we will control for this variable in the regression models. While the main hypotheses will be tested using ITT analysis, we will also conduct per protocol analysis only for patients who complete the treatment. Completed treatment is defined as (the infant) having received 70 % of planned doses. However, this will be considered supplemental and exploratory, and the results will not be used as main conclusions of the study.

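### The NEC endpoint requires radiological evidence and has no route for NEC proven at operation, on pathology or at autopsy; whether free air alone counts is unclear

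*Protocol article*

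**What the plan says.** The definition is in the protocol article, Methods/Design, under the outcome measures for specific Aim 1. The endpoints are introduced as "Secondary endpoints: NEC and death". NEC then requires modified Bell's "criteria stage > 2 with clinical signs and radiological evidence", and the qualifying evidence is given as "clinical signs and radiological evidence including any of the following: pneumatosis intestinalis, portal venous gas with or without pneumoperitoneum".

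The Statistical analysis section makes NEC an outcome of the main model: "A multivariable logistic regression with L-OS or NEC or death as the dependent variable". It does not say whether the three outcomes are modelled separately or combined.

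The Background gives the expected frequency and the clinical weight of the disease: extremely premature infants have "the highest incidence (10–12 %) of NEC, as well as the highest NEC-associated mortality rates". It also describes the disease itself: "NEC is an inflammatory bowel necrosis which involves mucosal injury".

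Findings at operation, on pathology or at autopsy are mentioned neither in the definition nor elsewhere in the article.

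**The concern.** The Background describes NEC as necrosis of the bowel. Laparotomy, histology and autopsy show necrosis directly, whereas a film shows signs of it. The endpoint accepts the film and is silent on the direct evidence.

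Two kinds of infant have no clear place: one with free air alone on the film whose bowel is found necrotic at operation, and one who dies before a diagnostic film is taken and has bowel necrosis at autopsy. If such infants are not counted, NEC is under-counted. If each of five sites decides for itself, NEC is counted inconsistently. The gap remains whichever Bell stage threshold is intended.

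**Working it through.** **Reading the definition**

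1. The stage is joined by 'with' to clinical signs and radiological evidence, and those two are joined by 'and'. Stage alone does not suffice, and imaging is required.
2. The list names pneumatosis intestinalis and portal venous gas. Pneumoperitoneum follows 'with or without', so its presence or absence does not change the classification. It is not listed as a sign in its own right.
3. 'Including' may introduce an open list. Even so, it is an open list of radiological evidence. It could let free air in, but not an operative or autopsy finding.

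| Case | Result under the stated definition (stage met) |
|---|---|
| Pneumatosis or portal venous gas on film, with or without free air, with clinical signs | Counts |
| Free air alone on film, necrotic bowel at operation | Closed list: does not count. Open list: may count |
| Free air alone on film, isolated spontaneous perforation at operation | Closed list: does not count. Open list: may count, wrongly |
| No qualifying sign on film, necrosis at operation, on pathology or at autopsy | No route on either reading |

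Neither reading handles both free-air rows correctly.

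**The plan's own sample size**

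This figure concerns late-onset sepsis only: "Based on a 2-tailed alpha of 0.05 and 80 % power, a sample size of 498 (249 in each group) will be needed". For 20 % versus 10 %, with two-sided alpha 0.05 and 80 % power:

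n = [1.960·√(2·0.15·0.85) + 0.842·√(0.20·0.80 + 0.10·0.90)]² / 0.10² ≈ 199 per arm.

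Dividing by 1 − R² = 0.8 gives 248.75, so 249 per arm and 498 in total. Then 498/0.8 = 622.5, against 622 stated. The figures reproduce and do not depend on NEC. No power is stated for NEC.

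**How large could the NEC effect be?**

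From the article: incidence 10–12 %, 622 enrolled, 498 analysed. Assumed: the share m of cases without a named sign (5–30 %, equal in both arms), a treatment effect that halves NEC, no covariate adjustment, and that the 10–12 % includes such cases.

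- Expected cases among 622 before any treatment effect: 622 × 0.10 = 62 to 622 × 0.12 = 75.
- Cases at risk of being missed: 62.2 × 0.05 = 3 to 74.6 × 0.15 = 11 for m of 5–15 %; up to 74.6 × 0.30 = 22 for m of 30 %.
- Power with 249 per arm, two-sided 0.05, comparing p(1 − m) with 0.5·p(1 − m):

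| m assumed | Control events (p = 10–12 %) | Power |
|---|---|---|
| 0 | 24.9–29.9 | 56–65 % |
| 5 % | 23.7–28.4 | 54–62 % |
| 10 % | 22.4–26.9 | 52–60 % |
| 20 % | 19.9–23.9 | 47–55 % |
| 30 % | 17.4–20.9 | 42–49 % |

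**Bias**

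If the same share is missed in both arms, the risk ratio is unchanged, because (1 − m) cancels. The odds ratio, which the plan reports, barely moves. At 10 % versus 5 % it is (0.05/0.95)/(0.10/0.90) = 0.474. With m = 10 % it is (0.045/0.955)/(0.09/0.91) = 0.476.

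**The case against.** The strongest case on the other side has four parts.

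- **The wording is not closed.** The staging system governs, and 'including' can introduce examples. This stands for free air, where the text is ambiguous rather than exclusive. It does not supply an operative or autopsy route, because the requirement is still radiological.
- **Requiring specific imaging protects specificity.** Isolated free air may be a spontaneous perforation, so not listing it is defensible, and a diagnostic endpoint may be narrower than the disease. This stands: the Background description does not contradict the endpoint. But specificity is no reason to leave out necrosis that has been seen directly.
- **The article is condensed.** It refers to a fourth protocol version and a codebook, neither shown, which may classify such cases. That is possible. The article nevertheless states the required evidence, so its wording would still need correcting.
- **The consequence is small.** One definition serves both arms, and treating staff, investigators and the data analyst are blinded. This stands.

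A reader might go further and infer that the severest cases drop out of the endpoint. The documents do not support that. Severe, perforated or fatal cases with pneumatosis or portal venous gas count, and nothing shows that the remaining cases are the most severe. Fatal cases also count under the separate death endpoint, though not as NEC. Nor does any text instruct that the unlisted cases be recorded as free of NEC. That is what literal application yields when no route exists.

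**Conclusion.** The point holds as a defect in the stated definition of a secondary endpoint. NEC documented at operation, on pathology or at autopsy, without radiological evidence, cannot enter the endpoint as written, and the status of free air alone is ambiguous.

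The expected harm is a modest, non-differential under-count and inconsistent classification across sites. Its size is not computable from the article, and the 5–30 % range is an assumption with no documentary basis. Under the illustration, the loss is about 2–5 percentage points of power if 5–10 % of cases are missed, in an endpoint whose power starts at only 56–65 %.

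No bias between arms is shown; that rests on the share missed being equal in both arms. Late-onset sepsis and the sample size are untouched. An infant who survives surgery for NEC without a named sign might be counted under neither secondary endpoint. This merits correction but does not threaten the trial's main conclusion.

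**What to change.** Add to the NEC definition: 'or NEC documented at operation, on pathology or, where performed, at autopsy, irrespective of radiographic signs'. State that isolated pneumoperitoneum counts only when operation or pathology shows NEC rather than an isolated spontaneous perforation.

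Have someone blind to arm make the classification, so not the site research nurse who assigns groups and prepares syringes. Apply one rule at all five sites, including to infants already enrolled, and complete it before unblinding.

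The cost is a short addition to the text and a small amount of extra record review. Outcome data are already collected until discharge or death, although the article does not say whether operative, pathology or autopsy reports are captured. Autopsy will not be available for every death, so some fatal cases may stay unclassified.
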